#### Data security and confidentiality

All data will be anonymised before entering data manually into an electronic data capture interface. All information will remain confidential and anonymised within the study team. Participant-specific data will be entered into the electronic data capture interface using only study IDs. Only the personal identifier of participants’ date of birth will be included in the database. In ensuring data quality and validity, the entered data will be double-checked by the person entering the data, and random checks will be performed regularly to ensure data validity. The statistical analyses will be conducted on anonymised data.

To anonymise the data, each participant will be assigned with a unique identification number (ID number), and no participant identifying information will be stored alongside data. The ID number with personal information will be safely stored separately from the trial data in order to secure confidentiality. Consent forms will be stored separately from participant data. The ID number will be used to administer and track all data collection, stored separately from data collection tools and locked in a secure room with limited access permissions. In ensuring the long-term preservation of the data generated in this study, the data files will be stored on secure password-protected university servers that are backed up daily, and access is restricted to researchers with passwords. Data generated via online survey software will be downloaded in spreadsheet format at least twice weekly. Data will be checked regularly to ensure the accuracy of data capture. All data will be uploaded to the password-protected university servers.

### Statistical methods

Differences in changes over time between the intervention and comparison groups will be assessed for each outcome. General linear model repeated measure analysis will be used to determine differences between groups over time (baseline, 3-month, and 9-month) with adjustment for potential covariates. Intention-to-treat (ITT) principles will be applied for parametric data. All participants will be analysed in both intervention and control groups regardless of whether they attended all data collection time points or completed the intervention [22]. The intention-to-treat principle is useful to preserve the sample size by including all randomised respondents regardless of noncompliance or withdrawal. The principle will be used to lower the probability of reduced statistical power due to the dropouts excluded from the final analysis.

Descriptive statistics (percentages or mean ± SD) will be calculated to describe participants’ sociodemographic characteristics and scores for each outcome measured by treatment and control groups. Repeated measures Analysis of Covariance (ANCOVA) will be performed to determine significant differences between groups at the 3- and 9-month surveys. The measures analyses will be controlled for covariate variables known to influence the outcome measures (child gender, parent education level, parent age, and parent income) [22]. The significance level will be set at ≤ 0.05. Analyses will be performed using Statistical Product and Service Solutions (SPSS; version 25.0; IBM, Armonk, NY, USA).

As randomisation will be at the school (cluster) level, the primary analysis will be adjusted for the clustering effect and the baseline value of the outcomes [63, 64]. Subgroup analysis will be performed to determine the direction of intervention effects by socioeconomic status, sex, and weight status. Where appropriate, multiple imputation methods will be used to account for missing data [18].

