### Sample size

The sample size is calculated for the primary outcome, BMI z-score. The sample size for individual randomisation of the present study is based on Formula 1 [29]. The values used in the sample size calculation are based on the BMI z-score data from Ahmad et al. (2018) [30] study, which is 1.95±0.45 and 2.09±0.35 for the treatment and control groups, respectively. Based on Formula 1, a calculated sample size required for each group arm is 131 child-parent dyads. It is calculated that, with at least 80% power to identify a small to medium effect size [31] at the 5% significance level, the present study needs a total of 262 child-parent dyads for the two-group arm.

$${}^{n}Individual\_Binary=\frac{{\left(z_{1-\frac{\alpha }{2}}+z_{1-\beta }\right)}^{2}[\sigma_{trt}^{2}+\frac{\sigma_{con}^{2}}{r}]}{\Delta^{2}}$$
(1)

**where**, $r=\frac{n_{con}}{\sigma_{con}},\Delta =\mu_{trt}-\mu_{con}$

*μ*_*trt*_ = Mean in treatment group = 1.95

*μ*_*con*_ = Mean in control group = 2.09

*σ*_*trt*_ = SD. in treatment group = 0.45

*σ*_*con*_ = SD. in control group = 0.35

*z* = Critical *z* value for a given Alpa (*α*) = 0.05 (two − sided) and Beta (*β*) = 0.2 with the value of $z_{1-\frac{\alpha }{2}}$ = 1.96 and *z*_1−*β*_ = 0.84

*r* = Ratio of the two sample sizes = 1/1

An adjustment using the design effect (DE) is made for the calculated sample size to allow for the design structure (due to the cluster sampling method), which results in larger sample sizes [32]. Taking into account unequal cluster size [10], assume the mean cluster size of 38 child-parent dyads will be recruited per preschool. Based on the Formula 2 [32, 33], given that the number of individuals per cluster (*n*) in the present study is 38 child-parent dyads and the Intra-cluster correlation coefficient (*ρ*) from the previous studies is 0.01 [18, 34], the calculated design effect of the present study is 1.37.

Designeffect(DE)=1+(n–1)ρ
(2)

By considering the design effect is 1.37 and the sample size required for each group arm (^*n*^Individual_Binary) is 131 (see Formula 3), the total sample size of the individual randomisation is further increased from 262 to 360 child-parent dyads.

$$({}^{n}Individual\_Binary)\times Design\;effect\times 2$$
(3)

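### The models named for every outcome have no random preschool effect, so they cannot deliver the cluster adjustment that the same section promises; the scope of that adjustment and the role of baseline are also unclear

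*Protocol article*

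**What the plan says.** Statistical methods describes the analysis in three steps.

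- First paragraph, covering all outcomes: "General linear model repeated measure analysis will be used to determine differences between groups over time (baseline, 3-month, and 9-month"). Covariates are to be included.
- Second paragraph: "Repeated measures Analysis of Covariance (ANCOVA) will be performed to determine significant differences between groups at the 3- and 9-month surveys". The covariates are the child's gender and the parent's education, age and income. Preschool is not listed. The threshold follows: "The significance level will be set at ≤ 0.05".
- Third paragraph: because schools are randomised, "the primary analysis will be adjusted for the clustering effect and the baseline value of the outcomes". No method for this adjustment is named. Subgroup analyses by socioeconomic status, sex and weight status follow, without mention of clustering.

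The abstract repeats the general linear model plan and does not mention clustering. Trial design and Sample size make clear that preschools are the randomised units, six per arm. Sample size also plans for clustering: "assume the mean cluster size of 38 child-parent dyads will be recruited per preschool", with an ICC of 0.01 and a design effect of 1.37.

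**The concern.** Allocation is by preschool, and part of the intervention is delivered in the classroom. The arm effect therefore has to be judged against variation between preschools. General linear model repeated measures and repeated-measures ANCOVA judge it against variation between children, so whoever runs the analysis must give up either the named model or the promised adjustment.

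Two further points in the same section are unsettled. The primary analysis could mean the analysis of BMI z-score or the main analysis of every outcome, and on the first reading the secondary outcomes have no stated cluster adjustment. Baseline is one of three levels of the time factor in the first paragraph and an adjustment variable in the third; these are different models with different arm contrasts.

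At stake are standard errors that are too small and a false-positive rate above the stated 5%.

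**Working it through.** **Inputs from the protocol.** Two-sided alpha 0.05 ("at the 5% significance level"); BMI z-score "1.95±0.45 and 2.09±0.35 for the treatment and control groups"; 38 dyads per preschool; ICC 0.01; six preschools per arm; 20% loss to follow-up.

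**The protocol's own chain.**
- Per arm: (1.96 + 0.84)² × (0.45² + 0.35²) / 0.14² = 7.84 × 0.325 / 0.0196 = 130.0, or 130.15 with unrounded z values, hence 131 as stated.
- Design effect: 1 + (38 − 1) × 0.01 = 1.37, as stated.
- Total: 131 × 1.37 × 2 = 358.9 (stated 360). After loss: 360 / 0.8 = 450 (stated 460). Clusters: 460 / 38 = 12.1 (stated 12).

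The chain reproduces closely enough, so 1.37 is the protocol's own measure of clustering.

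**Type I error of a single-time, unadjusted comparison that ignores preschool.** The true standard error is √DE times the naive one, so the error rate is 2 × (1 − Φ(1.96 / √DE)).
- 38 per preschool: DE = 1.37, 1.96 / 1.170 = 1.675, giving 9.4%.
- After 20% loss, 38 × 0.8 = 30.4 per preschool: DE = 1 + 29.4 × 0.01 = 1.294, 1.96 / 1.138 = 1.723, giving 8.5%.

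The ICC is the input that matters most. Other values are assumptions, since the protocol gives only 0.01. At 38 per preschool, 0.005 gives 7.2%, 0.02 gives 13.7%, 0.03 gives 17.7% and 0.05 gives 24.6%.

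**The tests the protocol names.** The formula above does not describe a test of change or a baseline-adjusted test, so these were simulated under no arm effect: 12 preschools of 38, ICC 0.01, 2,000 runs per setting. Two inputs are assumptions: a within-child correlation over time of 0.8, and the share of the preschool effect that is constant over the visits. Rejection rates at nominal 5%:

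| Test | All constant | 80% constant | 50% constant |
|---|---|---|---|
| Group-by-time, no preschool term | 5.2% | 11.0% | 20.6% |
| ANCOVA at 9 months, no preschool term | 5.7% | 9.0% | 15.9% |
| ANCOVA at 9 months, fixed preschool nested in arm | 5.7% | 9.1% | 16.5% |
| Preschool-level t-test on baseline-adjusted residuals, 10 df | 5.5% | 4.9% | 5.9% |

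The simulation error near 5% is about √(0.05 × 0.95 / 2000) = 0.5 percentage points.

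A preschool effect that is the same at every visit cancels from change over time and is largely removed by baseline adjustment. Only the part that varies between visits inflates these tests. The nested fixed factor does no better than no preschool term at all, because its error term is still the child. The preschool-level test stays near 5% throughout.

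**The case against.** The protocol does not overlook clustering. It raises the sample size for it and commits to adjusting for it, so inflation of the primary test follows only if the named models are run as written. That stands, and it makes the type I error figures conditional. It does not remove the conflict, because the section names no model that could honour the commitment. A full analysis plan might name one, but the contradiction is in the text shown.

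Four stronger readings are tempting, and the document does not support them.

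- **That the tests run far above 5%.** The only stated ICC gives 8.5-9.4%. Rates of 15-25% need an ICC of 0.03-0.05 or a preschool effect that varies strongly between visits, and the protocol states neither.
- **That secondary outcomes are deliberately left unadjusted.** The term is undefined, the sentence speaks of outcomes in the plural, and its reason (randomisation by school) applies to all of them. The text is ambiguous and does not exclude them.
- **That a fixed preschool factor makes the arm effect impossible to estimate.** With preschool nested in arm, an arm contrast of preschool means can be computed. The fault is the error term.
- **That including baseline as a time level dilutes the effect.** This would apply to an arm effect averaged over all three visits. The protocol asks for differences in change over time and differences at 3 and 9 months, so it does not name that contrast.

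**Conclusion.** The concern holds as a conflict within Statistical methods. The models named for each outcome cannot provide the cluster adjustment that the third paragraph promises, and a fixed preschool factor does not repair them. It is also unclear whether the adjustment reaches the seven secondary outcomes and the subgroup analyses, and baseline has two incompatible roles.

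If clustering were ignored, the cost on the protocol's own ICC and cluster size is a type I error of about 9.4% for a single-time comparison, or 8.5% after the planned loss. For the tests of change and the baseline-adjusted tests it is about 5-6% if the preschool effect is constant over time, and about 9-11% if 80% of it is; both shares are assumed. The conflict itself does not depend on these assumptions; only the size of the inflation does.

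**What to change.** Replace both named models by one linear mixed model, and state that it applies to every outcome, primary and secondary:

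- responses: the 3- and 9-month values;
- fixed effects: arm, visit, arm-by-visit, the baseline value of the outcome (as a covariate only) and the four covariates already listed;
- a random preschool effect, and correlation between visits within child;
- small-sample inference suited to 12 clusters, such as Satterthwaite degrees of freedom.

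A preschool-level, baseline-adjusted analysis on about 10 degrees of freedom (12 preschools less two arms) would serve equally well. The subgroup analyses should use the same structure.

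The cost is a change of wording, a different procedure in the same software, and wider but correct standard errors. For a preschool-level test on 10 degrees of freedom without baseline adjustment, take the planned difference of 0.14, an SD of √((0.45² + 0.35²) / 2) = 0.403 and ICC 0.01. Power is then about 81% with 38 per preschool and about 75% with 30.4.

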After estimating a loss to follow-up of 20% for this trial, the final sample size is increased to a total of 460 child-parent dyads (230 per group arm). Thus, based on the total number of participants in the two groups is 460 and the number of individuals per cluster is 38 child-parent dyads (see Formula 4), a calculated number of preschool clusters in the present study is 12 preschools. Therefore, 6 preschool clusters will be randomised to each experimental and control group.

$$n\_cluster=\frac{Total\;number\;of\;participants\;in\;the\;two\;groups}{number\;of\;individuals\;per\;cluster}$$
(4)

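### The plan promises to analyse every randomised dyad, but ties intention-to-treat to parametric data and names a method that by default drops any dyad with a missed visit, so it permits a completer analysis

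*Protocol article*

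**What the plan says.** All the analysis statements are in the protocol article under Statistical methods.

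- **Scope of intention-to-treat:** "Intention-to-treat (ITT) principles will be applied for parametric data".
- **Who is analysed:** the next sentence reads "All participants will be analysed in both intervention and control groups regardless of whether they attended all data collection time points or completed the intervention". The one after describes the principle as "including all randomised respondents regardless of noncompliance or withdrawal". The section then gives a reason: to avoid losing power by leaving dropouts out.
- **Method:** "General linear model repeated measure analysis will be used to determine differences between groups over time (baseline, 3-month, and 9-month"), and in the following paragraph "Repeated measures Analysis of Covariance (ANCOVA) will be performed to determine significant differences between groups at the 3- and 9-month surveys". The software is SPSS 25. The primary analysis is also to be adjusted for clustering and for the baseline value.
- **Missing data:** the last sentence of the section says that, where appropriate, "multiple imputation methods will be used to account for missing data". It does not say when imputation is appropriate or whether it covers the primary outcome.

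The Sample size section expects dropout: "After estimating a loss to follow-up of 20% for this trial", the total is raised to 460.

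**The concern.** There are two faults.

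First, intention-to-treat defines who is analysed and in which arm. It has no link to the distribution of an outcome. Restricting it to parametric data makes the analysis set depend on a judgement made after the data are seen, and it conflicts with the sentence that follows. Activity and screen time are recorded in parent-reported minutes, which are often skewed (general experience, not a statement in the protocol), so the clause could matter for those outcomes.

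Second, the classical repeated-measures GLM needs a value at baseline, 3 months and 9 months. A dyad with one visit missing is deleted whole. By itself this method cannot keep the promise to analyse everyone whatever visits they attended, and the protocol expects one dyad in five to be lost.

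What is at stake is the randomised comparison. Parents in the intervention arm are asked to complete 13 modules of about 60 minutes each; control parents receive weekly newsletter messages. Unequal or selective dropout is plausible, though the protocol gives no figure for it. Deletion would also discard the 3-month value of any child who misses only month 9, although the 3-month comparison is part of the primary objective.

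**Working it through.** **Inputs (Sample size section):** means 1.95 and 2.09, difference 0.14; SDs 0.45 and 0.35; two-sided 5% level; 80% power; mean cluster size 38; ICC 0.01; 20% loss; 460 dyads in 12 preschools.

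**The plan's own figures**

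- Per arm: (z for 0.975 + z for 0.80)² × (0.45² + 0.35²) / 0.14² = (z sum)² × 0.325 / 0.0196. This gives 130.15 with unrounded z values, so 131 as stated.
- Design effect: 1 + (38 − 1) × 0.01 = 1.37.
- Total: 131 × 1.37 × 2 = 358.9 (stated as 360).
- Loss: 360 / 0.80 = 450. The stated 460 is slightly larger and within 3%.

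**Dyads left under complete-case deletion**

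- The same 20% miss both follow-ups: 460 × 0.80 = 368; 92 are dropped.
- 20% miss each follow-up independently (an assumption): 460 × 0.80 × 0.80 = 294.4; about 166 are dropped.

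**Power**

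For N dyads analysed, the mean cluster size is m = N/12, the design effect is DE = 1 + (m − 1) × 0.01, and the effective number per arm is n = N / (2 × DE). The standard error is √(0.325 / n), and power = Φ(0.14/SE − 1.96).

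| N analysed | m | DE | n effective | SE | 0.14/SE | Power |
|---|---|---|---|---|---|---|
| 460 (full information) | 38.33 | 1.373 | 167.5 | 0.0441 | 3.18 | 89% |
| 368 | 30.67 | 1.297 | 141.9 | 0.0479 | 2.93 | 83% |
| 294.4 | 24.53 | 1.235 | 119.2 | 0.0522 | 2.68 | 76% |

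If the design effect is held at 1.37 instead, power at 368 is 81%. For other assumed rates of complete loss, 10% leaves 414 dyads (about 86%) and 30% leaves 322 (76% to 79%).

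The 89% is a ceiling. No method recovers full information from absent visits.

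**The case against.** The strongest reply is that imputation is planned. A repeated-measures GLM run on imputed data includes every randomised dyad, and a fair reader may take the imputation sentence as the means of keeping the promise. The protocol nowhere states listwise deletion; that is the default behaviour of the classical procedure. Adjustment for clustering also suggests that the final model may not be the plain procedure. This stands as far as it goes. A reader might infer that the result will be a completer analysis, and the document does not support that. What remains is that the imputation is conditional, and nothing ties it to the primary analysis. Asking for that tie is not asking for imputation-model detail, which may properly sit in an analysis plan not shown here.

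A second reply is that BMI z-score is continuous and modelled parametrically, so intention-to-treat applies to the primary outcome on the plan's own wording. That is correct: the clause threatens secondary outcomes only. Even there, no non-parametric method is named, and the plan does not say that such outcomes would lose intention-to-treat. The wording merely leaves them uncovered.

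A third reply concerns size. A reader might infer that the trial becomes underpowered. At the planned loss it does not: 368 exceeds the 360 required. The 76% needs 20% missing at each visit independently, whereas the protocol gives a single 20% for the trial. A t reference with 10 degrees of freedom would give about 75% at 368 and 68% at 294, but it lowers power even with no dropout (about 82% at 460). That is a separate matter of having few clusters and should not be charged to deletion.

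**Conclusion.** The point holds as an internal contradiction. The protocol commits to analysing everyone, limits that commitment by an unsound rule, and names a method that by default breaks it. The only remedy it offers is left optional.

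At the planned 20% loss, complete-case analysis would remove about 92 of 460 dyads and leave power at about 83% (81% with the design effect fixed at 1.37), above the 80% target. Power falls below target only under heavier or scattered loss, such as 294 dyads and 76% under the independence assumption. These figures take the protocol's SDs, difference and ICC as given, use its normal-based formula, and assume that losses are spread evenly over 12 preschools.

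The main harm is possible bias if dropout is related to arm and outcome. Its size cannot be computed from the document. The loss of valid 3-month data arises only for children who attend month 3 and miss month 9; it does not arise if the same dyads miss both visits.

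**What to change.** 1. Delete the restriction to parametric data and state that intention-to-treat applies to every outcome. Handle a skewed outcome by its method of analysis, on the same set of dyads.
2. Replace the repeated-measures GLM with a likelihood-based mixed model that uses every available 3- and 9-month value, with preschool as a random effect and adjustment for baseline. Alternatively, commit the primary analysis to multiple imputation that respects the clustering by preschool.
3. Name the other approach as the sensitivity analysis. With baseline as a covariate, the mixed model gains nothing from a dyad with neither follow-up visit, so imputation is what keeps those dyads in the analysis.

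The cost is a few sentences in Statistical methods and a little more analysis work. No extra data collection or change of sample size is needed.

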### Sociodemographic and participant characteristics

Parents will be asked questions about their child’s participation. Parents will be asked to proxy-report general information about their family unit. Sociodemographic information of each child and his/her family will be collected by adapting questions in the general information section of the validated Preschool-age Physical Activity Questionnaire (Pre-PAQ) [48], which includes a child’s sex, ethnicity, date of birth, the number of children under 18 years old living in the household, the language spoke at home, household income, parents’ aged, education level, current working status, and current marital status. Household incomes will be categorised into 3 groups based on the income classification of Malaysia: Ringgit Malaysia (RM) 4,849 and less; RM 4,850 to RM 10,959 and; RM 10,960 and over [49]. The survey will be conducted at baseline only.

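### The subgroup aim is the direction of the effect in each stratum, which does not test whether the effect differs between strata

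*Protocol article*

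**What the plan says.** One sentence in Statistical methods covers subgroups: "Subgroup analysis will be performed to determine the direction of intervention effects by socioeconomic status, sex, and weight status". It is not limited to the primary outcome, BMI z-score. The article says no more about a model, a comparison between strata, a rule of interpretation or the exploratory status of these analyses.

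The same section gives a general threshold, "The significance level will be set at ≤ 0.05", in the paragraph before, after the repeated-measures analysis of covariance. It is not tied to subgroups. The primary analysis is to be adjusted for clustering and for the baseline value.

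Socioeconomic status is not defined for the subgroup analysis. The section on sociodemographic characteristics says "Household incomes will be categorised into 3 groups based on the income classification of Malaysia". It also collects parental education and working status, and links none of these to the subgroups.

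The sample size rests on the overall comparison of BMI z-score only.

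**The concern.** The useful question in a subgroup analysis is whether the effect differs between strata, and its null hypothesis is equal effects. The sign in each stratum answers another question. Two strata with the same true effect can show opposite signs by sampling error alone, and two strata with truly different effects can share a sign. An analysis plan that followed the stated aim faithfully would carry this weakness with it. The point therefore concerns the aim that is written, and does not depend on detail being absent.

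At stake is how the results are read. The section on significance and outlook suggests that the education ministry might adopt the programme if it proves efficacious. A chance reversal in one sex or income group could be taken as a reason to direct it to some families and not others. The risk is greatest where effects are small or absent. That is realistic for at least some of the seven secondary outcomes, for which no effect size is given.

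**Working it through.** **Inputs (Sample size section).** The BMI z-score inputs are given as "which is 1.95±0.45 and 2.09±0.35 for the treatment and control groups, respectively", so the planned difference is 0.14 and the variance sum is 0.45² + 0.35² = 0.325. The protocol adds that the intra-cluster correlation "from the previous studies is 0.01 [18, 34], the calculated design effect of the present study is 1.37". There are 6 preschools per arm.

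**The protocol's own figures.** (1.96 + 0.84)² × 0.325 / 0.14² = 130.0, or 131 after rounding up with unrounded z values; the protocol states "a calculated sample size required for each group arm is 131 child-parent dyads". Then 131 × 1.37 × 2 = 358.9, and the protocol states that "the total sample size of the individual randomisation is further increased from 262 to 360 child-parent dyads". The inputs are thus confirmed. I take 360 dyads as analysed: 180 per arm, 30 per preschool.

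**Assumptions not in the document.** Sexes are split 50/50. Income stands for socioeconomic status, in three groups split as equal thirds, 70/20/10 or 70/25/5. There is no baseline adjustment. Weight status is left out of the arithmetic, because its strata are formed on the BMI z-score itself and no SD within them is given.

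**Chance of sign disagreement under a uniform effect d.** For a stratum with nᵢ children per arm:

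SEᵢ² = (0.325 / nᵢ) × [1 + (nᵢ/6 − 1) × 0.01], pᵢ = Φ(d / SEᵢ), P(signs not all equal) = 1 − Πpᵢ − Π(1 − pᵢ).

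- Sex: nᵢ = 90, SE = √(0.325/90 × 1.14) = 0.064. At d = 0.14, p = 0.985 and P = 2 × 0.985 × 0.015 ≈ 2.9%. At d = 0.07, p = 0.862 and P = 2 × 0.862 × 0.138 = 24%. At d = 0, P = 50%.
- Income, equal thirds: nᵢ = 60, SE = √(0.325/60 × 1.09) = 0.077. At d = 0.14, p = 0.966 and P = 1 − 0.966³ − 0.034³ = 9.9%.

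The formula treats strata as independent. Simulations in which strata share the preschool effect give slightly lower values:

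| Uniform true effect | Sex, formula | Sex, simulated | Income, formula | Income, simulated |
|---|---|---|---|---|
| 0 | 50% | 46–48% | 75% | 70–72% |
| 0.07 | 24% | 21–23% | 45–54% | 43–52% |
| 0.14 | 2.9% | 3% | 10–28% | 9–28% |

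The income ranges span the assumed splits.

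**Interaction test for sex.** In simulated data with no true sex difference it rejects in 4.9–5.2% of trials. The SE of the difference between two sex-specific effects is √(2 × 0.325/90 × 0.99) = 0.0846; the shared preschool effect cancels. For a true sex difference of 0.14, power is Φ(0.14/0.0846 − 1.96) = 38%. The difference detectable with 80% power is 2.8 × 0.0846 = 0.24.

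**The case against.** The strongest objection is that the sentence states a purpose and no decision rule. Direction by sex can be read from an interaction model as well as from separate strata, and the model, confidence intervals and exploratory label are ordinary content of an analysis plan that is not shown. This stands in part. A reader might infer that the protocol will declare a subgroup difference whenever signs differ, or that it will often do so falsely. It does not say so, and at the planned effect the sexes would disagree in only about 3% of trials.

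A reader might also apply the 0.05 threshold within each stratum. At 0.14 the power per sex would be Φ(0.14/0.064 − 1.96) ≈ 0.59, so one sex would be significant and the other not in about 2 × 0.59 × 0.41 = 48% of trials. The arithmetic is sound, but the protocol plans no such within-stratum test, so this figure does not measure a fault in it.

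Three further objections have weight:

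- **Baseline adjustment lowers the figures when there is a real effect.** With an assumed baseline correlation of 0.5 to 0.8, the variance falls by the factor 1 − r². Sex disagreement at 0.07 drops from 24% to 19–7%, and at 0.14 to 1.2% or less. At zero effect it stays at 50%.
- **The income figures rest on assumptions**, both in the split and in taking income as socioeconomic status.
- **The largest figures belong to a programme with no effect**, which would hardly be proposed for wider use on its primary outcome.

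An interaction model would not change the stratum signs either; it changes what is concluded from them. What the objection does not remove is that the one stated target of the subgroup analysis does not compare strata.

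**Conclusion.** The point holds in a limited form. Direction by stratum is the wrong target for judging whether the effect varies, and the protocol names it as the aim. The practical risk depends on the true overall effect. It is material when that effect is absent or well below 0.14: 21–48% for sex and 43–72% for three income groups at uniform effects of 0.07 down to 0. At 0.14 it is about 3% for sex and 9–28% for income, against about 5% for an interaction test. These figures rest on the protocol's SDs and intra-cluster correlation, 360 analysed dyads, assumed stratum splits and no baseline adjustment.

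The documents do not support the statement that the trial will make false subgroup claims; they leave that risk open. Severity is minor, since subgroups are in no objective and played no part in the sample size.

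**What to change.** Replace the subgroup sentence with wording such as: *Differences in the intervention effect by socioeconomic status, sex and baseline weight status will be estimated with treatment-by-subgroup interaction terms in the same cluster- and baseline-adjusted model, using all participants. Stratum-specific effects will be shown with 95% confidence intervals. Subgroup differences will be judged from the interaction and not from the sign or significance within a stratum. These analyses are exploratory.*

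This keeps all three planned factors. The variable that defines socioeconomic status should be named at the same time.

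The cost is one sentence and a few model terms, with no extra data or participants. The drawback is low power: about 38% for a sex difference as large as the whole planned effect. The trial will therefore support few subgroup statements, which is a fair reflection of its size.
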